## Methods

### Trial design

The FAGOTTO trial is a multicenter, open-label, randomized (1:1), parallel-group study aimed at clarifying the effects of canagliflozin on renal hemodynamics and its safety in patients with type 2 diabetes and moderate DKD. This trial has been registered in the Japan Registry of Clinical Trials (jRCTs041200069). The study protocol was approved by the Certified Review Board of Nagoya University Graduate School of Medicine (No. CRB4180004). All patients will provide written informed consent to participate in this study after they receive information about the purpose of the study as well as the potential risks and benefits. Additional consent will be also confirmed for use of participant data and biological specimens in future ancillary study.

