### Intervention and control

Eligible participants will be randomly assigned (1:1) to the canagliflozin or control group. After a run-in period of up to 4–8 weeks, the canagliflozin group patients will be administered canagliflozin 100 mg orally once daily in the morning for 12 weeks. In contrast, in the control group, glucose levels will be controlled without any SGLT2i. Inulin and para-aminohippuric acid (PAH) clearance tests for the measurement of renal hemodynamics will be performed at baseline and 4 weeks after the start of the trial. A change in the type or dose of prior diabetic drugs and antihypertensive drugs is prohibited during the 12-week intervention period, but if side effects such as hypoglycemia and hypotension occur, reduction of the dose or discontinuation of these drugs is allowed. The use of the following drugs is restricted during the 12-week intervention period: diuretics, drugs that enhance the hypoglycemic effect, including β-blockers, salicylic acid agents, and monoamine oxidase inhibitors.

The study flowchart is shown in Fig. 1.

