### Sample size

For the purpose of comparing independent results, we decided to use power of 0.85 and a significance level of 0.05, to detect a significant difference. The difference in the percentage change in FF after 4 weeks of treatment in the canagliflozin group compared with that in control group was assumed to be 60% of the standard deviation. Based on these calculations, we determined that at least 50 individuals are necessary for each group. Taking into account potential discontinuation and withdrawal, we set the target number for the canagliflozin group to 55, with 55 control patients, and thus, 110 patients were planned to be included in total. Additionally, we took into account the actual number of patients who met the registration criteria at each facility.

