### Statistical analyses

Validity/safety will be analyzed in the largest analysis target group (full analysis set; FAS), defined below. To be included in the FAS, subjects must satisfy these two criteria: (1) meet the selection criteria and not meet the exclusion criteria, and (2) have at least one marker to evaluate efficacy after administration (regardless of the primary or secondary endpoint). The primary aim of the analysis is to compare the percentage changes between the canagliflozin group and the control group at 4 weeks after administration using analysis of covariance (ANCOVA) with eGFR, proteinuria, age, and HbA1c as covariates. No interim analysis is planned.

The analysis methods for secondary outcomes are shown in Table 2.

**Table 2 Tab2:** Analysis methods for secondary outcomes of the canagliflozin and control groups

Secondary outcomes	The analysis methods
1. Percentage change and the change in eRPF, eRBF, and RVR after 4 weeks of treatment	• Compare the percentage changes between the canagliflozin group and the control group at 4 weeks after administration by analysis of covariance (ANCOVA) with eGFR, proteinuria, age and HbA1c as covariates
2. Change in FF, eRPF, eRBF, and RVR after 4 weeks of treatment	• Compare the percentage changes between the canagliflozin group and the control group at 4 weeks after administration by analysis of covariance (ANCOVA) with FF, eRPF, eRBF, and RVR at the baseline and eGFR, proteinuria, age, and HbA1c as covariates
3. Changes in eGFR, HbA1c, albuminuria after 4 weeks and 12 weeks of treatment, trend of blood pressure and body weight after 4 weeks and 12 weeks of treatment, and change in urinary angiotensinogen levels after 4 weeks of treatment	• Calculate the adjusted mean and the 95% CI for changes at each time point by a linear mixed model with each treatment group, time point, and interaction of the treatment group and time point as the fixed effects • Compare between treatment groups using a linear mixed model with values of each index at baseline, treatment groups, time points, interaction between treatment groups and time points as the fixed effects and changes of each index as response variables • Compare changes of each index among treatment groups at each time point using the Tukey–Kramer method to correct for multiplicity
4. Rate of adverse drug reactions	• Calculate the 95% confidence interval for each treatment group and compare it between the groups using χ2 test (or Fisher's exact test)

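### As written, the Tukey–Kramer step in Table 2, row 3 corrects for no multiplicity, because with two arms it is the same as the unadjusted t-test at each time point

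*Protocol article*

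**What the plan says.** The design has two arms. The Trial design section describes a "multicenter, open-label, randomized (1:1), parallel-group study", and the Intervention and control section says: "Eligible participants will be randomly assigned (1:1) to the canagliflozin or control group".

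Table 2 in the Statistical analyses section sets out the secondary analyses. The label of row 3 begins "Changes in eGFR, HbA1c, albuminuria after 4 weeks and 12 weeks of treatment, trend of blood pressure and body weight after 4 weeks and 12", where the quote is cut, and it ends with urinary angiotensinogen at week 4. The row therefore covers five indices at two post-baseline time points and a sixth at one.

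The between-group comparison uses a linear mixed model with baseline value, group, time point and "interaction between treatment groups and time points as the fixed effects and changes of each index as response variables". The last step in the row is: "Compare changes of each index among treatment groups at each time point using the Tukey–Kramer method to correct for multiplicity".

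The article names no other multiplicity method.

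**The concern.** Tukey–Kramer protects the error rate over all pairwise comparisons among several group means. The row defines that family as the treatment groups, separately at each time point. With canagliflozin and control as the only groups, the family holds one comparison, so there is nothing to protect against.

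The multiplicity that does exist in this row comes from testing at weeks 4 and 12 and from testing six indices. The step reaches neither. Readers of the results could take p-values labelled as Tukey–Kramer-corrected for eGFR, HbA1c, albuminuria, blood pressure and body weight as protected, when each is an ordinary test at the full 5% level.

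**Working it through.** **Inputs.**
- Two arms (Intervention and control).
- Weeks 4 and 12 for eGFR, HbA1c, albuminuria, blood pressure and body weight; week 4 only for urinary angiotensinogen (Table 2, row 3).
- Significance level 0.05 and power 0.85: "we decided to use power of 0.85 and a significance level of 0.05, to detect a significant difference" (Sample size).
- Difference in the primary endpoint: "was assumed to be 60% of the standard deviation" (Sample size).
- The correlation between the week 4 and week 12 tests is not given. It is assumed, with a range of 0 to 0.9.

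**1. The plan's own figure.** The article gives no figure for the Tukey–Kramer step. The one figure that can be recomputed is the sample size: "we determined that at least 50 individuals are necessary for each group". With a two-sided 0.05:

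n per group = 2 × (1.960 + 1.036)² / 0.6² = 2 × 8.98 / 0.36 = 49.9, so 50.

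This reproduces. The same formula with a one-sided 0.05 gives 40, so the stated level is taken as two-sided below. (The noncentral t gives 50.9, with power 0.844 at 50 per group, which is close enough.)

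**2. Tukey–Kramer with two groups.** For groups of size n1 and n2 with pooled variance s²:

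q = |mean1 − mean2| / √[(s²/2)(1/n1 + 1/n2)] = √2 × |t|.

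Hence the Tukey–Kramer critical value divided by √2 is the two-sided t critical value, for equal or unequal group sizes.

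| Degrees of freedom | Tukey–Kramer, 2 groups (q/√2) | Unadjusted t, two-sided 0.05 |
|---|---|---|
| 96 (illustrative) | 1.98498 | 1.98498 |
| 98 (50 + 50 − 2) | 1.98447 | 1.98447 |
| 108 (55 + 55 − 2) | 1.98217 | 1.98217 |

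On one simulated data set with groups of 55 and 50, both methods give p = 0.046512. In the mixed model, the step returns the t-test of the group contrast at that time point, adjusted for baseline but not for multiplicity.

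**3. Error rate left over weeks 4 and 12.** For one index with no treatment effect at either time point, the chance of at least one false positive is 1 − P(|Z1| ≤ 1.96 and |Z2| ≤ 1.96), with Z1 and Z2 bivariate normal with correlation r.

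| Assumed r | Chance of at least one false positive |
|---|---|
| 0 | 1 − 0.95² = 0.0975 |
| 0.3 | 0.095 |
| 0.5 | 0.091 |
| 0.7 | 0.083 |
| 0.9 | 0.070 |

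**4. What a correction would require.** Bonferroni over two time points tests each at 0.05 / 2 = 0.025. The critical value at 98 degrees of freedom is then about 2.28 instead of 1.98.

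**The case against.** The strongest defence is that the step could mean something else. It follows a model with a group-by-time interaction. If Tukey–Kramer were run over all four group-by-time means (six pairs) and the two between-group contrasts were then read off, it would adjust: the critical value is about 2.61 at 98 degrees of freedom, or about 0.0104 per comparison. The article is condensed and the analysis plan is not shown, so this cannot be excluded as the intention. It is not what is written, however, because the row confines the comparison to treatment groups within each time point. If the four-mean family was meant, the sentence still needs changing, since the two readings give thresholds of 1.98 and 2.61. Nor is this a detail left to the analysis plan: the article names both a method and its purpose, and the method cannot serve that purpose.

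It is also fair to say that secondary outcomes need no multiplicity correction. That stands. The fault is the claim of a correction that the method does not deliver.

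Two stronger readings may tempt a reader, and the document supports neither.
- **That the plan promises a correction over time points.** The row gives multiplicity as the reason without naming its source. Time points are an inference, reasonable because within one index nothing else remains to correct.
- **That the error rate is 43%.** The row has 5 × 2 + 1 = 11 comparisons, counting blood pressure as one index, and 1 − 0.95^11 = 0.431. This needs eleven independent tests with every null hypothesis true. Weeks 4 and 12 are measured in the same patients, and the Background section itself expects this drug class to improve glycaemic control and to lower weight, blood pressure and albuminuria. The figure is not a realistic size for the problem.

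**Conclusion.** The point holds for the text as written. In a two-arm trial, Tukey–Kramer among groups at each time point is the unadjusted t-test. That is an algebraic identity and rests on no assumption about the data. The consequence is that an index with two time points carries a false-positive chance of about 7% to 9.75% when there is no effect, rather than 5%; that range does rest on the assumed correlation. Urinary angiotensinogen has one time point and so no such inflation within the index, but the correction is empty there too. Multiplicity across the six indices is also unaddressed.

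The reach is limited. A reader might infer that the trial's main conclusion is at risk; it is not. The percentage change in filtration fraction at week 4 is a single primary endpoint with its own ANCOVA, and neither that test nor the sample size depends on this step. Estimates and nominal intervals for the row 3 outcomes also stay as they are; what is wrong is the label on their p-values. The change should be made, as a matter of accurate reporting of secondary results.

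**What to change.** Change the last step of Table 2, row 3 in one of two ways, before these outcomes are analysed:

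1. Remove the statement that multiplicity is corrected. Report the between-group comparisons at each time point as unadjusted, exploratory p-values with nominal 95% confidence intervals.
2. Replace Tukey–Kramer with Holm (or Bonferroni at 0.025) over weeks 4 and 12 within each of the five indices that have both time points. State that urinary angiotensinogen has a single comparison and that no adjustment is made across indices.

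Either is a one-line edit. The first costs nothing statistically. The second makes some secondary p-values slightly larger: under Bonferroni the critical value at 98 degrees of freedom rises from about 1.98 to about 2.28, and Holm applies that threshold only to the smaller of the two p-values, testing the other at 0.05 if the first is significant. Neither option changes the primary analysis or the number of patients.

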### Dissemination

Nagoya University Graduate School of Medicine will submit results of this study to a peer-reviewed journal on the basis of own judgment from a scientific and neutral standpoint with complying confidentiality obligations.

## Discussion

Several large-scale randomized control studies have provided evidence of the cardioprotective and renoprotective effects of SGLT2i [13]. Among them, a randomized clinical trial of empagliflozin was the seminal study. The trial was designed to assess the cardioprotective effect of empagliflozin in type 2 diabetic patients with > 7.0% of HbA1c and a high risk of CV events [14]. It demonstrated that patients who received empagliflozin had lower rates of hospitalization for heart failure as well as CV and all-cause mortality [8]. The authors also demonstrated renoprotective effects as the secondary microvascular outcome of this trial included a significant relative risk reduction of doubling of serum creatinine level and initiation of renal replacement therapy in patients whose eGFR was at least 30 ml/min/1.73 m^2^ [9]. Notably, eGFR of the empagliflozin group showed a short-term decrease in the first 4 weeks and remained stable from long-term administration to the end of the trial, while that of the placebo group declined steadily [9]. Next, a convincing report from the integrated CANVAS program showed that canagliflozin prevented the progression of albuminuria and renal events; specifically, findings showed a 40% reduction in eGFR, renal replacement therapy, or renal death in type 2 diabetic patients with inadequate glycemic control and an elevated risk of CV diseases with a mean eGFR of approximately 76 ml/min/1.73m^2^ [15, 16]. There was the CREDENCE trial designed primarily to assess the renoprotective effect of canagliflozin in patients with type 2 diabetes [17]. In this trial, the inclusion criteria specified patients with type 2 diabetes with over 6.5% of HbA1c and risk factors for the progression of kidney disease, such as albuminuria, who were treated with renin-angiotensin system blockade; enrollment included approximately 60% patients with stage 3 CKD [17]. Although the subjects in the CREDENCE trial had low eGFR at the start in contrast to those included in the previous CV outcome trials of SGLT2i [9, 16], canagliflozin showed similar effects, including a lower risk of end-stage renal disease, doubling of serum creatinine level, or death from renal causes, compared to placebo [18]. Based on these clinical trials, the renoprotective effect of SGLT2i is now recognized, but the magnitude of its effectiveness in individual patients remains unclear. A systematic review reported that the renoprotective effect of SGLT2i was greater in diabetic patients with preserved renal function at baseline than in those with moderate CKD, whereas the cardioprotective effect was greater in patients with poorer renal function [13]. Although an eGFR dip is observed in the eGFR curve after prescribing SGLT2i, a recent editorial indicated that a larger dip generally resulted in a stronger benefit of SGLT2i than placebo [19]. Thus, to demonstrate whether SGLT2i can modulate renal hemodynamics even in patients at high risk of end-stage renal disease, our trial will evaluate renal hemodynamics during an eGFR dip in patients with moderate renal dysfunction who are administered SGLT2i.

The possible renal protective effects of SGLT2i are diverse, including lowering blood pressure via natriuresis and osmotic diuresis, reducing hypoxia in the proximal tubule via tubular workload reduction, and anti-inflammation-fibrosis action [20–22]. Among these actions of SGLT2i, correction of intraglomerular hypertension via restoration of tubular glomerular feedback is thought to be the most crucial and dynamic [21]. An experimental study in an animal model of type 1 diabetes demonstrated that SGLT2i induced afferent arteriolar vasoconstriction and decreased the single-nephron glomerular filtration rate via the tubule-glomerular feedback mechanism that resulted in the reduction of intraglomerular pressure, using in vivo multiphoton microscopy imaging techniques [23]. Cherney et al. demonstrated that SGLT2i attenuated glomerular hyperfiltration in patients with type 1 diabetes mellitus with glomerular hyperfiltration defined by eGFR ≥ 135 mL/min/1.73 m^2^; attenuation of glomerular hyperfiltration was accompanied by a decrease in renal blood flow and an increase in renal vascular resistance [10]. The authors discussed that such a reduction of glomerular hyperfiltration was mediated by preglomerular vasoconstriction by affecting the tubular-glomerular feedback mechanism, and long-term use of SGLT2i might reduce intraglomerular pressure, resulting in an overt renoprotective effect [10]. Interestingly, this trial failed to show this evidence in patients with normal glomerular filtration [10]. Recently, van Bommel et al. conducted a trial to evaluate the renal hemodynamic effect of SGLT2i in patients with type 2 diabetes mellitus with eGFR ≥ 60 mL/min/1.73m^2^ treated with metformin monotherapy [11]. They showed that SGLT2i lowered the mGFR without increasing renal vascular resistance, and these effects were accompanied by postglomerular vasodilation [11]. Interestingly, the ability to lower postglomerular resistance was independent of blood glucose concentration [11]. Although clinical studies have demonstrated a renoprotective effect of SGLT2i in patients with type 2 diabetes who have moderate renal dysfunction, as discussed above, changes in renal hemodynamics after SGLT2i administration in these patients are still unclear. This trial will contribute to research in the field by elucidating the renal hemodynamic mechanism of SGLT2i and, provide a significant basis for the prescription of SGLT2i in patients with DKD if we demonstrate its ability to control intraglomerular pressure in our subjects.

The target number of patients is 110 (1:1 = canagliflozin group: control group). This protocol was approved by the Certified Review Board of the Nagoya University Graduate School of Medicine on November 6, 2020 (Version 1.2), and opened to the public on the website of the Japan Registry of Clinical Trials on November 27, 2020. We enrolled the first patient on December 23, 2020. By the end of June 2022, we enrolled 81 patients from three participating hospitals and further recruitment is ongoing. This study is expected to end in 2025. The FAGOTTO study is the first randomized controlled study of canagliflozin to assess renal hemodynamics in patients with type 2 diabetes and moderate renal dysfunction. Although further studies will be needed, the data from this study will provide evidence for optimal therapy to prevent progression of DKD.

## Data Availability

Not applicable.

## Abbreviations

ALT: Alanine aminotransferase
ANCOVA: Analysis of covariance
AST: Aspartate aminotransferase
CVD: Chronic kidney disease
CV: Cardiovascular
DKD: Diabetic kidney disease
ESRD: End stage-renal disease
FF: Filtration fraction
GFR: Glomerular filtration rate
PAH: Para-aminohippuric acid
RBF: Renal blood flow
RPF: Renal plasma flow
SGLT2i: Sodium-glucose cotransporter 2 inhibitors
